### Case manager training

One three-hour training session program informed by the literature and consultation with experts [45-48], will be delivered at the beginning of the program. The training introduces case managers to the aim and importance or need for LEAP and trains them in setting SMART (Specific; Measurable; Achievable; Relevant: Timely) goals [49]. The training will conclude with a brain storming session on specific strategies that could be used to fully implement LEAP within their organisation. Strategies will be fed back to each site to review, collectively finalise and action.

### Care worker training

Care workers will participate in four two or three hour training sessions, held every three months. The staggered sessions will allow time to apply and consolidate sessions and act as boosters to continue using the principles of engagement taught in LEAP. Training has been designed to be delivered on-site to small groups of between 6–10 case managers or 10–20 care workers.

Care worker training was developed based on the following principles and psychosocial strategies for which there was an evidence base in improving outcomes: taking a person-centred individualised approach [50], dementia and the unmet needs model of challenging behaviours [23], communication skills [51], autonomy and control [52,53], reminiscence [54,55], music [56], physical activity [57], Montessori activities [58] humour [59] and reciprocity [60].

Over the course of the training program, the LEAP Champion will also accompany each care worker on a buddy visit to a client in order to support care workers in practising client engagement techniques. Training materials will be translated into Chinese and delivered by a trilingual trainer (English, Mandarin, and Cantonese) in a Chinese speaking site.

### Inducting new staff members

Staff turnover in home care is high [40]. LEAP champions will review and discuss LEAP for Life with care workers who missed training sessions, using a provided script and handout of key points. New case managers will also attend a brief training session.

### Evaluation

The study has been approved by the University of New South Wales Human Research Ethics Committee (HC12383) and registered on the Australian New Zealand Clinical Trials Registry (ACTRN12612001064897).

### Setting

The project will be evaluated with five aged care community service providers in regional and metropolitan New South Wales, Australia. The providers were approached to participate by the chief investigator. Two of the sites specifically provide services for clients from ethnic minority, non-English speaking backgrounds. These services deliver case managed home care packages. The types of services provided by these packages include personal care, domestic assistance, social support, travel to appointments, in-home respite and nursing care.

Eligibility criteria for participating services are:

• Government accredited, providing home care packages to older people in the community;

• Not enrolled in another intervention study relating to engagement and activities;

• Willing to sign a legal contract with regards to program terms.

### Study participants and recruitment processes

1) *Case managers and care workers*

Site managers or their nominees will invite all staff members working on home care packages to participate in the study and provide them with a study flyer, information sheet and consent form. Care workers will either be paid for their time participating in the evaluation or receive a small inducement to complete questionnaires. Based on discussions with site managers, we anticipate that all of the 20 case managers and 90% of the 183 care workers (i.e. 165) will consent to participate.

2) *Community aged care clients*

All eligible clients (*n* = approximately 422) being cared for by the service under a home care package will be invited to participate. A 50% participation rate and 25% attrition is anticipated, thus about 211 clients will be recruited, and 158 clients will provide complete client data over 18 months. Clients will be ineligible if they are; foreshadowed to stop accessing the service, acutely unwell, or under public guardianship with no person responsible to consent on their behalf.

Case managers or their nominee will invite all eligible clients to participate in the evaluation by briefly introducing the study and giving them and/or their families a study flyer. Clients and their families will give verbal assent to case managers to have their details passed onto the research team who will explain the study and provide a written information and consent form. Cognitively intact clients and families will each provide written consent for their own participation. When the client may be cognitively impaired, verbal assent will be obtained from the client, and family written consent will be obtained for both family and client participation.

### Design

LEAP is being evaluated using a quasi-experimental design with measurements taken at -6, 0 (baseline immediately pre-intervention), 6 and 12 months. The time period from -6 to 0 months will act as non-intervention comparison for the period between 0, 6 and 12 months. Clients will be clustered under their case managers (*n* = 20).

#### Assessment tools

##### Primary outcome measure: client engagement

Client engagement will be assessed from both the care worker and client perspective. A six-item purpose-specific care worker questionnaire will measure the five dimensions of engagement conceptualised in Cohen-Mansfield’s Observational Measure of Engagement (OME) - for which there has been demonstrated sound inter-rater reliability and construct validity [61]. The five dimensions are: client rate of refusal of offers of interaction; proportion of time during care worker visits that the client is involved with an activity or conversation; client attention level; client attitude towards any interaction; and the appropriateness of client interaction. In order to ascertain test-retest reliability of the measure, 20 care workers will be asked to complete the questionnaire twice, two weeks apart.

Client perspectives on engagement with care staff will be rated by researchers after conducting semi-structured interviews with the clients and families. Researchers will rate four engagement items pertaining to frequency of and feelings towards social conversation or recreational activities during care worker visits. A random selection of 10 interviews shall be scored by a two researchers, in order to establish inter-rater reliability.

##### Secondary outcome measures

Secondary outcome assessment tools for both client and care worker are detailed in Table 2.

**Table 2 T2:** Secondary outcome measures for client and care staff and the covariates

	**Measure**	**Data collection method**
Client secondary outcome		
Agitation	34-item Cohen-Mansfield Agitation Inventory-relative[62]	Family self-report
	13-item Agitation subscale of The Neuropsychiatric Inventory – Clinician Rating Scale [63]*	Client/family interview
Dysphoria/depression	15-item Geriatric Depression Scale [64]^†^	Client self-report
	13-item Dysphoria subscale of The Neuropsychiatric Inventory- Clinician Rating Scale [63]*	Client/family interview
Loneliness	20-item Revised UCLA Loneliness Scale [65]‡	Client self-report
Apathy	18-item Apathy Evaluation Scale – self and informant [66]	Client and family self-reports
	11-item Apathy subscale of The Neuropsychiatric Inventory - Clinician Rating Scale [63]*	Client/family interview
Satisfaction with care	9-item care worker subscale and 13-item case manager subscale of the Home Care Satisfaction Measure [67]	Client self-report
Client Covariates	age; gender; care site; hours and type (i.e. CACP, EACH or EACH-D) of packaged care; duration of package; the presence (or absence) of a cohabiting carer; number and hours of care from non-paid carers; dementia or mental health diagnoses; ethnicity; language spoken; education; previous employment; significant life events/functional change as reported by case manager; case manager; client and care worker positive interaction measured by the 8-item positive relationship subscale of the Caregiver Interaction Scale completed by the family [68]; happiness measured by the 8-item Jovality subscale and 4-item attentiveness subscale of the PANAS-X client self-report (completed once in reference to the time scale of the past two weeks and once in reference to during care worker visits) [62]; severity of cognitive impairment as measured by the Global Deterioration Scale [69]; two items assessing importance to client and family that care workers engage socially with the client; country of birth; years lived in Australia; English proficiency; income; living situation; relationship of family member; relationship between care worker and client as measured by the 4-item Bond subscale of the Working Alliance Inventory Short Form client report [70]	Client/family self-report
		Care plan audit
		Case manager interview
		Client/family interview
Care worker secondary outcome		
Work satisfaction	5-item dedication subscale of the Utrecht Work Engagement Scale [71]	Care worker self-report
Care staff covariates	age; gender; care site; hours of work; duration of employment in current role and in the aged care industry; name of manager; education; ethnicity; language spoken; diversional therapy or lifestyle experience; number of clients/staff supported; relationship between care worker and client as measured by the 4-item Bond subscale of the Working Alliance Inventory Short Form care worker self-report [70]; case manager work satisfaction measured by the 5-item dedication subscale of the Utrecht Work Engagement Scale [71]; country of birth; years lived in Australia; English proficiency; duration of relationship with client; number and duration of care visits to clients over two weeks.	Care staff self-report

*Note*. Translations will be made of all questionnaires, other than those individually noted above where pre-existing translated versions are available.

*Pre-existing translated versions in Spanish and Chinese are available.

^†^Pre-existing translated versions in Spanish, Vietnamese and Arabic are available.

‡Pre-existing translated versions in Arabic and Spanish are available.

##### Translations

Assessments will be conducted in English, Cantonese, Mandarin, Vietnamese, Arabic or Spanish according to the preferred language of participants. Validated translated versions of scales will be used where available (see Table 2). Where they are not available (See Table 2), scales will be translated by accredited translators, then checked for meaning by bilingual research staff with experience in the area.

#### Process evaluation

The process evaluation will assess five components [72,73].

#### Context

Aspects of the environment or organisation that may influence intervention implementation or study outcomes (such as perceived or real barriers, enablers, organisational culture, management support, and attitudes of care staff, clients and families towards LEAP), will be established through interviews with case managers at each evaluation time-point; monthly phone meetings with the LEAP Champions; and bi-annual steering committee meetings.

#### Reach

Care staff attendance at each LEAP training session, and the number of LEAP inductions conducted with new care staff, shall be recorded.

#### Dose delivered

LEAP is a semi-scripted manualised program with set learning objectives, activity aims, activities, handouts and timings. Information about whether each component of the manual is delivered will be recorded. Number of buddy shifts conducted shall also be recorded.

#### Dose received

The extent to which the care staff actively engage with the LEAP program and implement the strategies and activities learnt in training shall be documented by way of case manager interviews, and phone meetings with the LEAP Champion.

A care plan audit will identify whether a SMART social or recreational goal, a vague social or recreational goal, or no goal, has been included in the care plan for each client. The audit will also identify whether or not a personal history sheet documenting clients’ past and present interests, preferences, relationships, roles and so forth is included in the client’s file. Case manager interviews and the care plan audit will collectively inform: 1) how well the goal was (or is being) implemented for each client (0 – not started; 1 – planned; 2 – in progress; 3 – achieved); 2) whether other engagement strategies are being implemented with each client (ranging from 0 - none at all, to 4 - a lot); and 3) reasons if no social or recreational goal has been identified for a client.

Care workers will complete a one week activity diary recording frequency and type of social and recreational activities undertaken with clients.

#### Fidelity

The extent to which LEAP is implemented as planned, shall be established by way of case manager interviews, phone meetings with LEAP Champions, and a review at 12 months of the success of each site-specific implementation plan. In regards to the behaviour of the facilitators, care staff will complete a short written evaluation after each training session.

#### Power

The target sample of 211 clients clustered within 20 case managers will give at least 80% power to detect a small effect size (Cohen’s *d* = 0.2) at a significance level of two sided 0.05, assuming a median intraclass correlation (rho = 0.5) between pre and post intervention measures [74,75]. This power analysis is based on one group comparing pre- and post-measures for the primary outcome measure [75]. As the engagement score is a new measure, we do not know what the correlation structure among the repeated assessments using the instrument will be. Post hoc power analysis will be conducted upon study completion.

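### The stated power of at least 80% counts all 211 recruits as pre-post pairs; after the plan's own 25% attrition it is about 70–77% before clustering, and lower with it

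*Protocol article*

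**What the plan says.** The Power section of the protocol article reads: "The target sample of 211 clients clustered within 20 case managers will give at least 80% power to detect a small effect size". The effect is Cohen's d = 0.2, "at a significance level of two sided 0.05", "assuming a median intraclass correlation (rho = 0.5) between pre and post intervention measures". The comparison is specified: "This power analysis is based on one group comparing pre- and post-measures for the primary outcome measure". The same section adds that, because the engagement score is new, the correlation structure among repeated assessments is not known.

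The section on study participants and recruitment shows where 211 comes from. About 422 eligible clients are invited and half are expected to take part. It then applies 25% attrition: "thus about 211 clients will be recruited, and 158 clients will provide complete client data over 18 months".

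The Design section sets measurements at −6, 0, 6 and 12 months and says clients are clustered under 20 case managers. The Data analysis section analyses all enrolled clients and handles missing outcomes through the mixed model under missing at random. No case-manager ICC and no design effect is given anywhere in the article.

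**The concern.** A pre-post comparison draws its information mainly from clients measured on both sides. The recruitment section expects a quarter of clients to be lost, yet the power figure rests on the count before that loss. The two sections therefore disagree about how much data the comparison will have.

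The power sentence also names the 20 case-manager clusters, so it reads as if clustering had been allowed for. The only correlation supplied is called an intraclass correlation but is defined between pre and post measures. It is a within-client quantity and says nothing about how alike clients of the same case manager are.

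This is the only power justification given for the primary outcome. If it is too favourable, a null result would be read as stronger evidence against a small effect than the study can supply.

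**Working it through.** **Inputs.** From the Power section: d = 0.2, ρ = 0.5, two-sided α = 0.05, n = 211, 20 case managers. From the recruitment section: 422 × 0.50 = 211 recruited; 211 × 0.75 = 158.25, so 158 with complete data.

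**Step 1: the plan's own figure.** The standardised change is δ = d/√(2(1 − ρ)) = 0.2/√1 = 0.2. Power ≈ Φ(δ√n − 1.96).
- n = 211: Φ(2.905 − 1.96) = 82.8%; noncentral t gives 82.4%. This agrees with at least 80%.
- Pairs needed for 80%: ((1.960 + 0.8416)/0.2)² = 196.2, so 197 (199 by noncentral t).

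**Step 2: attrition, complete pairs only.** n = 158: Φ(2.514 − 1.96) = 71.0%; noncentral t gives 70.5%.

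**Step 3: attrition, partial records used.** Suppose the other 211 − 158 = 53 clients give only a pre value. In SD units, the variance of the estimated mean change under maximum likelihood is (1 − ρ²)/n_post + (1 − ρ)²/n_pre = 0.75/158 + 0.25/211 = 0.00593. Then z = 0.2/√0.00593 = 2.60 and power = Φ(2.60 − 1.96) = 73.8%.

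**Step 4: a later-loss variant.** The 158 are complete over the whole 18 months, so some of the lost clients will still have a month-6 value. If loss is even over time (assumption), 211 × (1 − 0.25 × 12/18) = 175.8, about 176.
- Complete pairs, n = 176: 75.6% (noncentral t 75.1%).
- With pre-only records: variance 0.75/176 + 0.25/211 = 0.00545, z = 2.71, power 77.3%.

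**Step 5: clustering.** Only clustering of the change matters, because a stable case-manager effect cancels within a client. The design effect is DE = 1 + (m − 1) × ICC, with m = n/20.
- Largest DE compatible with 80% at n = 211: 211/196.2 = 1.075. With m = 10.55, ICC = 0.075/9.55 ≈ 0.008.

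Power by the normal approximation, with all non-zero ICC values assumed:

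| ICC of change | 211 pairs | 158 pairs |
|---|---|---|
| 0 | 82.8% | 71.0% |
| 0.01 | 79.3% | 68.1% |
| 0.02 | 75.9% | 65.4% |
| 0.05 | 66.6% | 58.2% |

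For example, at 158 and ICC 0.05: m = 7.9, DE = 1 + 6.9 × 0.05 = 1.345, effective n = 158/1.345 = 117.5.

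**Step 6: other readings.**
- Taking ρ = 0.5 as a case-manager ICC gives DE = 5.775 at n = 211, effective n 36.5 and about 23% power. That cannot be how the stated figure was obtained.
- A one-sided test reaches 80.8% at 158, but the plan is two-sided.
- ρ = 0.6 reaches about 80% at 158, but the plan assumes 0.5. At ρ = 0.3 power is about 69% with 211 and 56% with 158.

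**The case against.** Four points deserve weight.

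First, 158 counts clients complete at all four waves, and the planned mixed model uses everyone enrolled. Complete-pair power on 158 is therefore a conservative figure. This stands, and it is why the range before clustering runs up to about 77%. Neither way of using partial records tried above reaches 80%.

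Second, there are two waves before and two after the start. With equal correlation of 0.5 between all waves (assumption), comparing the mean of two pre with the mean of two post measures has variance 0.5 instead of 1, so δ = 0.2/√0.5 = 0.283 and power at 158 without clustering is 94%. With one pre and two post measures it is 83%. But the Power section describes a plain pre-post comparison with a single ρ, and does not say that waves were averaged. This calculation shows that a different justification might have been written; it does not support the one that was.

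Third, a reader might infer that the authors used a design effect of exactly 1. The article does not show that. It prints at least 80%, not 82%, and a design effect up to 1.075 would fit. What can be said is that the figure leaves almost no room for one.

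Fourth, the text does define ρ as a pre-post correlation and admits that the correlation structure is unknown, and an article may leave an ICC table to a fuller document. That is fair as far as it goes. It does not explain why the attrition stated in the same article is absent from the power figure.

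**Conclusion.** The point holds as a correction to the power statement. With d = 0.2, ρ = 0.5 and a two-sided 5% level, the stated power needs about 197 complete independent pairs, and the plan expects 158 clients with complete data. For the comparison the Power section describes, power before clustering is about 70% on complete pairs, about 74% with pre-only records, and about 75–77% if even loss leaves roughly 176 clients with a month-6 value. Clustering of change would lower each of these by an amount the article does not allow one to fix.

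A reader might go further and say that true power is 58% to 74%. The documents do not support that. The lower figure combines complete cases with an assumed ICC of 0.05; the upper one is a mixed-model figure with no clustering. They are different calculations, not the ends of one range. Nor does the finding show that more clients must be recruited, since all eligible clients of the services are already invited.

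The attrition result rests on the plan's own inputs. The 176 clients and every non-zero ICC are assumptions.

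**What to change.** Rewrite the Power section in three respects.

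1. State power after the expected attrition and drop the at-least-80% claim. Suggested wording: about 70–77% for d = 0.2 and ρ = 0.5 before clustering, depending on how partial records are used, and lower with clustering of change.
2. Describe ρ simply as the within-client pre-post correlation. Give the case-manager ICC of change separately, with a sensitivity range labelled as assumed, such as 0.01 to 0.05.
3. Say which waves form the pre and post measures. If the calculation averaged more than one wave on either side, give that calculation in full with its correlation assumption, attrition and clustering.

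The cost is a reworded paragraph and a less favourable figure. No extra clients are needed, and neither the design nor the analysis changes.

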**Methods/design:**

The 12 month LEAP program has three components: 1) engaging site management and care staff in the program; 2) employing a LEAP champion one day a week to support program activities; 3) delivering an evidence-based training program to care staff. Specifically, case managers will be trained and supported to set meaningful social or recreational goals with clients and incorporate these into care plans. Care workers will be trained in and encouraged to practise good communication, promote client independence and choice, and tailor meaningful activities using Montessori principles, reminiscence, music, physical activity and play. LEAP Champions will be given information about theories of organisational change and trained in interpersonal skills required for their role. LEAP will be evaluated in five home care sites including two that service ethnic minority groups. A quasi experimental design will be used with evaluation data collected four times: 6-months prior to program commencement; at the start of the program; and then after 6 and 12 months. Mixed effect models will enable comparison of change in outcomes for the periods before and during the program. The primary outcome measure is client engagement. Secondary outcomes for clients are satisfaction with care, dysphoria/depression, loneliness, apathy and agitation; and work satisfaction for care workers. A process evaluation will also be undertaken.

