#### Data analysis

Piecewise linear mixed effect models will be used as the primary analysis method, with correlations between repeated measurements taken into account. The mean and standard deviation of the pre-intervention slope (-6 to 0 months) and post intervention slope (0 to 12 months) as well as the mean outcome measure at time 0 with 95% Confidence Interval will be estimated. The difference of the two slopes will be tested based on the Z score at the significance level of two-sided 0.05. The model will be fitted with and without covariates. Piecewise least squares analysis will be conducted as supportive analysis. The primary analysis will be performed on the qualified intention to treat (ITT) population of all the clients enrolled in this study. Missing outcome data will be handled by the mixed effect model approach, providing the missing at random (MAR) assumption is met. If appropriate, multiple imputation will be used to generate missing covariate data. Quantitative process evaluation data shall be described. Qualitative process evaluation data shall be described and where appropriate, thematically analysed. Where possible, analyses will also be conducted using process evaluation data as predictors of outcomes.

An estimate of LEAP program costs will be made. This will be based on the costs of both delivering and staff attending the training, time for the LEAP champion, and the cost of any materials or resources required for activities.

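### The stated power of at least 80% belongs to a one-group pre-post comparison, not to the primary test of a difference between two slopes

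*Protocol article*

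**What the plan says.** The Power section of the protocol article starts from "The target sample of 211 clients clustered within 20 case managers" and says that this "will give at least 80% power to detect a small effect size", with d = 0.2, two-sided alpha 0.05, and "assuming a median intraclass correlation (rho = 0.5) between pre and post intervention measures". It then gives the comparison behind the figure: "This power analysis is based on one group comparing pre- and post-measures for the primary outcome measure [75". It adds that the correlation structure of the new engagement measure is unknown and that power will be examined again after the study.

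The Data analysis section names a piecewise linear mixed model as the primary method, with one slope from -6 to 0 months and another from 0 to 12 months. The test is: "The difference of the two slopes will be tested based on the Z score at the significance level of two-sided 0.05". The Design section sets the visits at -6, 0, 6 and 12 months and makes the first interval the non-intervention comparison. The abstract says the same in general terms: "Mixed effect models will enable comparison of change in outcomes for the periods before and during the program".

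The recruitment section expects about 211 clients, of whom 158 would have complete data over 18 months.

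**The concern.** The powered quantity and the tested quantity differ. A pre-post comparison asks whether the mean has moved since baseline and makes no use of the -6 month visit. The primary test asks whether the rate of change after time 0 differs from the rate before it. It therefore subtracts a pre-intervention slope that rests on one six-month interval, and the noise in that slope enters the test.

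The trial has no control group, so the slope comparison is its only internal control. A reader of the Power section would take 80% as the chance that this test detects a small effect. If the chance is much lower, a non-significant primary result says little about whether an effect of the planned size was present, yet the stated figure invites the opposite reading.

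**Working it through.** **Inputs from the protocol.** n = 211 recruited and 158 complete; d = 0.2; correlation rho = 0.5; two-sided alpha 0.05; visits at -6, 0, 6 and 12 months; slopes over -6 to 0 and 0 to 12 months.

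**Assumptions the protocol does not state.** The pre-intervention slope is zero, the gain after time 0 is linear, and the correlation is the same (0.5) between all pairs of visits. There are no random slopes. The visit at which d = 0.2 applies is not given, so two readings are shown.

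**Step 1: the plan's own figure.** The SD of a paired change is SD × √(2(1 − rho)) = 1 SD at rho = 0.5.
- n = 211: 0.2 × √211 = 2.905, and power = Φ(2.905 − 1.96) = 82.8% (82.4% with the noncentral t). The stated figure is reproduced; 197 clients would give 80%.
- n = 158: 71%.

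**Step 2: the variance of the primary contrast.** Fit a line with a knot at 0 to the four visits, in units of 6 months. The weights on visits -6, 0, 6 and 12 are:
- post slope: (0, −1/2, 0, 1/2)
- pre slope: (−1, 5/6, 1/3, −1/6)
- difference: (1, −4/3, −1/3, 2/3)

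Under constant correlation, the variance per client is (1 − rho) times the sum of squared weights. For the difference this is 0.5 × (1 + 16/9 + 1/9 + 4/9) = 0.5 × 3.333 = 1.667 SD². For the post slope alone it is 0.5 × 0.5 = 0.25 SD². Tested alone, for 0.2 SD at 12 months, the post slope would have the same 82.8% power as the paired test. The loss comes entirely from subtracting the pre slope, which multiplies the variance by 1.667/0.25 = 6.7.

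SE of the difference per 6 months: √(1.667/211) = 0.0889; √(1.667/158) = 0.1027.

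**Step 3: power of the primary test** (two-sided Z).

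| Reading of d = 0.2 | Slope difference per 6 months | n = 211 | n = 158 |
|---|---|---|---|
| 0.2 SD reached at 12 months | 0.1 SD | 20.3% | 16.4% |
| 0.2 SD at 6 months, continuing to 0.4 SD at 12 | 0.2 SD | 61.4% | 49.5% |

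For example, 0.1/0.0889 = 1.125, and Φ(1.125 − 1.96) plus the small opposite tail is 20.3%. With 211 enrolled and dropout spread over the visits, the first row gives about 18.7%. An AR(1) correlation of 0.5 per 6 months gives 19.6% and 15.8%.

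**Step 4: what 80% power does cover.** Detectable difference = (1.96 + 0.84) × √((1 − rho) × 3.333/n), in SD per 6 months; double it for the departure at 12 months. The last column is the power for 0.2 SD reached at 12 months.

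| rho | Detectable per 6 months, n = 211 / 158 | At 12 months | Power, n = 211 / 158 |
|---|---|---|---|
| 0.3 | 0.29 / 0.34 | 0.59 / 0.68 | 16% / 13% |
| 0.5 | 0.25 / 0.29 | 0.50 / 0.58 | 20% / 16% |
| 0.7 | 0.19 / 0.22 | 0.39 / 0.45 | 31% / 24% |
| 0.9 | 0.11 / 0.13 | 0.22 / 0.26 | 71% / 59% |

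On the second reading of d, power passes 80% only at a higher correlation than the plan assumes (83% at rho = 0.7 with 211 clients).

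**The case against.** The strongest reply is that nothing in the Power section is miscalculated. The section names its comparison openly, 82% is at least 80% under the stated rho, and the unknown correlation is admitted. This stands. The figure itself is correct, and the words at least can stay once the figure is tied to the pre-post comparison. Naming the basis does not, however, tell the reader that the primary test has much less power, and a power analysis after the study cannot repair the mismatch.

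A reader might infer that the primary test simply has 16 to 20% power and would miss the planned effect about four times in five. The documents do not support that as an unconditional statement. It needs d = 0.2 to be read at 12 months, with a flat pre-period and a linear gain. Because the test depends only on the slope difference, clients who decline by 0.1 SD per 6 months before the program and gain 0.1 SD per 6 months during it would also give 61%.

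The 158-client figures are pessimistic. The planned mixed model uses all enrolled clients, so those with partial data contribute.

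A reader might also infer that clustering under case managers makes matters worse. The contrast weights sum to zero, so a constant case-manager effect cancels. Only variation between clients or case managers in change over time would add variance, and the protocol gives no figure for that.

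Finally, the 211 follows from about 422 eligible clients and 50% participation, so the power figure did not set the sample size.

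**Conclusion.** Wrong as written: the stated power does not belong to the stated primary test. At the plan's own rho = 0.5, with a flat pre-period, a linear gain and constant correlation, the slope-difference test has about 20% power with 211 clients (16% as a lower bound with 158) if 0.2 SD is reached at 12 months. It has about 61% (49%) if 0.2 SD is reached at 6 months and the gain continues. Neither reaches 80%. How large the shortfall is depends on those assumptions; that there is one at rho = 0.5 holds on both readings.

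The point does not show an arithmetic error in the protocol, and it does not show that the design or the choice of primary test is invalid.

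**What to change.** Restate the Power section for the slope-difference contrast, with its assumptions on the pre-intervention slope, the shape of the gain and the correlation across visits. At rho = 0.5 it should say that 80% power is available for a slope difference of about 0.25 SD per 6 months with 211 clients, and up to 0.29 SD if only 158 contribute, which is about 0.50 to 0.58 SD at 12 months. Add a sensitivity range over rho, since the section itself says that the correlation structure is unknown. State the visit to which d refers. Keep the 80% for d = 0.2, but say that it applies only to a simple uncontrolled pre-post change.

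The cost is a rewritten paragraph and a less favourable stated figure. No extra clients, visits or data are needed. The rewording does not raise the power of the test; it lets a non-significant result be read for what it is.
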